### Statistical analysis

Upon completion of data collection, data will be cleaned and prepared for data analyses. Primary and secondary outcome variables and mediating mechanisms will be checked for distribution, outliers and missing patterns, and appropriate steps will be taken where necessary (cf., [57]). All analyses follow intention-to-treat principles, taking advantage of all available data points. Low levels of missings will be expected, with previous studies showing high completion rates (> 90%, e.g., [26]). Intermittent missing data will be handled by maximum likelihood (MI) estimation. Participants who completely drop out of the study will be treated as smokers. Preliminary analysis will include a randomization check to test for baseline differences between intervention and control participants. For the main data analysis, we will use multilevel modeling to account for the nested structure of daily measures within individuals [58]. To examine the first research question on the effects of the intervention using the daily diary, a set of generalized linear mixed models will be performed in SPSS and R. Daily smoking abstinence will be modeled as a function of time group and group by time, testing group differences at the quit date (model 1) and 3 weeks later (model 2) by centering the time variable accordingly. Model 3 will separately test group differences 6 months later. For the primary outcomes of subjectively and objectively reported smoking abstinence (dichotomous), we will use mixed logistic regression analyses. For the secondary outcome of subjectively reported number of cigarettes smoked, a count variable, we will use a negative binomial model with zero inflation [59, 60]. To test the third research question on the mediating mechanisms of the intervention effect, we will use a multilevel approach to mediation analysis based on multilevel structural equation models [61, 62].

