**Fig. 1 Fig1:**
[figure not shown]
The longitudinal study design

Participants of this randomized controlled trial are adult smokers, who smoke at least one cigarette daily [43], intend to quit smoking during the study, and own a smartphone with access to mobile internet. Moreover, participants should speak German fluently, should not work in 24-h shifts, should not participate in a professional smoking cessation program, and should not already use a smoking cessation smartphone app. Recruitment takes place in Switzerland and is organized via advertisements in newspapers, online platforms and on webpages, flyers and postings in the university, medical facilities and local companies. Interested individuals can complete a prescreening assessment online, for which they provide informed consent and that checks inclusion and exclusion criteria. In case smokers meet all inclusion criteria, they are contacted via email and sent the link for an online end-of-day diary questionnaire for three consecutive days (baseline diary).

After completing the baseline diary participants are contacted and invited to the lab for a background assessment. At the background assessment participants first receive full information on the study, and provide written informed consent. After completing a comprehensive background questionnaire, participants are asked to set a self-set quit date within the next 6 weeks. They are instructed to fill in the online challenge diary from 7 days before the self-set quit date, on the self-set quit date and 20 days after the self-set quit date. During those 28 days all participants receive a daily text message with the link for the questionnaire at seven o’clock in the evening. Subsequently, participants receive an instruction for the personal mobile objective smoking abstinence measure, the iCO Smokerlyzer (Bedfont Scientific Ltd.), and the corresponding smartphone app to measure the exhaled carbon monoxide (CO) daily. A first measurement of CO with the iCO Smokerlyzer is already taken in the lab. Lastly, participants of the intervention group are introduced to the smartphone app (for details on randomization procedure and the intervention see below). Six months after the self-set quit date, participants of both groups are contacted via email and asked to participate in the follow-up diary phase for completing online end-of-day diaries for three consecutive days and daily objective assessments of smoking with the iCO Smokerlyzer.

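### A skipped home CO test is left to maximum likelihood even when the same-day diary reports smoking, so objective abstinence can be overstated if tests are skipped more often on smoking days

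*Protocol article*

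**What the plan says.** The protocol article names two primary outcomes, daily self-reported abstinence and daily abstinence by exhaled CO (Aims of the present study). The Measures section has the diary smoking items and the CO reading collected together in the 28-day challenge phase and the 3-day follow-up. At 6 months, participants are asked for "completing online end-of-day diaries for three consecutive days and daily objective assessments of smoking with the iCO Smokerlyzer".

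The Statistical analysis section gives one model family: "For the primary outcomes of subjectively and objectively reported smoking abstinence (dichotomous), we will use mixed logistic regression analyses". Abstinence is modelled on time, group and their interaction, and for the last time point "Model 3 will separately test group differences 6 months later".

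Two missing-data rules apply to all outcomes:

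- "Intermittent missing data will be handled by maximum likelihood (MI) estimation"
- "Participants who completely drop out of the study will be treated as smokers"

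Around them stand a general principle ("All analyses follow intention-to-treat principles, taking advantage of all available data points"), an expectation of more than 90% completion based on earlier studies, and a promise that variables will be "checked for distribution, outliers and missing patterns, and appropriate steps will be taken where necessary". The section does not mention a missing CO reading on a day with a completed diary.

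**The concern.** The CO test is done at home on the participant's own phone, so each day the participant decides whether to blow. Someone who has just smoked has a reason to skip it. If that person still fills in the diary, the two rules produce an uneven result: a participant who vanishes is counted as smoking, while one who admits smoking but gives no reading is left missing.

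Maximum likelihood in a mixed logistic model is valid when missingness is ignorable given the data in the model. The diary answer is the most informative variable on whether a missing reading would have shown smoking, and the CO model is not stated to contain it. At 6 months the model is separate, so a participant with three diaries and no reading contributes nothing to the objective comparison.

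At stake are the level of objective abstinence in each arm and, if the arms skip differently, the treatment effect on a primary outcome whose purpose is to guard against misreporting.

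**Working it through.** **The plan's planning values.** Power analysis section: control 27%, difference 24 points, hence intervention 51%; two-sided 0.05, power 0.80. With pooled variance, n per arm = [1.96·√(2·0.39·0.61) + 0.842·√(0.27·0.73 + 0.51·0.49)]² / 0.24² = 63.7, so 64 and N = 128, as stated. This point does not depend on N; 27% and 51% serve as true rates below. True odds ratio: (0.51/0.49)/(0.27/0.73) = 2.81.

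**Formula.** Let p be true abstinence, and a and s the proportions of abstainers and smokers without a reading. Among those with a reading,

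observed = p(1−a) / [p(1−a) + (1−p)(1−s)].

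All values of a and s are assumptions; the article gives none. If a = s, observed = p and nothing is overstated.

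**1. Same skipping in both arms, whole person lost** (a = 10%, s = 30%)
- Control: 0.243/(0.243 + 0.511) = 32.2%
- Intervention: 0.459/(0.459 + 0.343) = 57.2%
- The difference moves from 24 to 25 points. Both odds are multiplied by (1−a)/(1−s), so the odds ratio stays 2.81.

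**2. Same rates, but daily and independent over three follow-up days, with stable smoking status.** All three readings must be missing: a³ = 0.001, s³ = 0.027.
- Control: 0.2697/(0.2697 + 0.7103) = 27.5%
- Intervention: 0.5095/(0.5095 + 0.4768) = 51.7%
- The shifts are 0.5 and 0.7 points.

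**3. Ceiling if 10% of each arm is missing, all of them smokers**
- Control: 0.27/0.90 = 30.0%
- Intervention: 0.51/0.90 = 56.7%
- This extreme implies that 0.10/0.73 = 13.7% of control smokers and 0.10/0.49 = 20.4% of intervention smokers skip, so it is itself arm-specific. The difference is 26.7 points and the odds ratio (0.51/0.39)/(0.27/0.63) = 3.05.

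**4. Skipping that differs by arm, whole person lost** (a = 5%)

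| Smokers skipping, control / intervention | Observed control | Observed intervention | Difference | Odds ratio |
|---|---|---|---|---|
| 10% / 30% | 28.1% | 58.5% | 30.5 points | 3.62 |
| 30% / 10% | 33.4% | 52.4% | 18.9 points | 2.19 |

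**5. Challenge phase, mixed model fitted by maximum likelihood.** This was a simulation with 80 per arm, 21 days, an assumed random-intercept SD of 2.5, 25 runs per scenario and 5% skipped on abstinent days.
- 20% skipped on smoking days: 28.4% rises to 30.0% (control) and 48.6% to 51.9% (intervention).
- 40% skipped on smoking days: 30.0% rises to 33.1% and 49.7% to 55.8%.

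In the 20% case the simple formula gives 30.5% and 55.3%, which is 3.5 and 4.3 points above truth, against 1.6 and 3.3 in the simulation. The random intercept recovers part of the loss, not all. With the same skipping in both arms the fitted log odds ratio moved from 1.60 to 1.72 and from 1.58 to 1.79. So few runs do not show whether this is more than noise, so the exactly unchanged odds ratio is claimed for the simple formula only.

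**The case against.** The strongest reply is that nothing in the article shows CO tests being skipped more often on smoking days, and without that there is no bias. This stands: a reader might infer that objective abstinence is overstated, but the documents support only that it can be.

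Second, the trial asks about group differences, and skipping that is alike in both arms leaves the odds ratio at 2.81 in the simple formula. This also stands. A reader might go further and infer a false benefit: with no true effect and 27% in both arms, 10% of abstainers, 20% of control smokers and 40% of intervention smokers without a reading would give 29% v 36%. Nothing in the article supports that split. Buddies take part only in the 28-day phase, app use is instructed for that phase, CO readings are not listed among what the app shows the buddy, and the lottery rewards completing follow-up, not abstinence. With daily independent skipping the same split gives 27.1% v 28.3%, about 1.2 points.

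Third, the 30%/10% example implies 0.27·0.10 + 0.73·0.30 = 24.6% missing in control, well above the plan's expectation. That expectation, however, rests on earlier studies, and the one cited as an example is described in the Background as a mobile-phone study of daily support and cigarettes smoked. The article calls this trial the first to assess abstinence objectively every day, so the 90% figure gives no direct assurance about device readings.

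Fourth, missing patterns will be checked, and the label MI may mean multiple imputation. The steps after that check are not named, the words say maximum likelihood, and no diary input is mentioned. Imputation using the diary would largely answer the point.

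Finally, detail on device data may sit in a fuller document. But the article does state rules here, and applied as written they set aside a known answer.

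**Conclusion.** The point holds in conditional form. As written, a participant who admits smoking but skips the CO test is treated as ignorably missing on an objective primary outcome, while a complete dropout counts as smoking.

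The size depends on skip rates that the documents do not give. With the same skipping in both arms, inflation ranges from under 1 point (independent daily skipping at follow-up) to about 5 and 6 points (30% of smokers and 10% of abstainers lost entirely). It is at most about 3 points in control and 6 in intervention if no more than 10% of each arm is missing. Material bias in the comparison needs arm-specific skipping among smokers and could go either way. The article makes this conceivable in the challenge phase, where only one arm has the buddy app, but does not document it. The documents do not support a stated overstatement or a stated false benefit at 6 months. The change is still worth making, because the diary data are already collected and the present rules are uneven.

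**What to change.** State a rule for missing CO readings that uses the same-day diary, by one of two routes:

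- **Preferred:** a multiple-imputation or joint model for CO abstinence that includes self-reported abstinence and number of cigarettes smoked. The text should then say whether maximum likelihood or multiple imputation is meant.
- **Simpler:** code a day with reported smoking and no CO reading as smoking, and leave challenge-phase days with reported abstinence and no reading to maximum likelihood.

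At 6 months, code participants with diaries but no CO reading on any of the three days as not verified abstinent, in line with the existing dropout rule. Add a sensitivity analysis coding all missing CO days as smoking; this also covers people who report abstinence and avoid the test, whom the diary cannot reveal. Report CO completion by arm and by self-reported status.

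The cost is a coding or imputation rule, one sensitivity analysis and one table, with no new data. Objective abstinence rates will be slightly lower, and some true abstainers who miss the follow-up tests will count as not verified. The simpler route has a small downward bias because only smoking days are filled in: in the simulation with 20% skipped on smoking days, control abstinence fell from 28.4% to 26.7% and intervention from 48.6% to 47.4%. The imputation or joint model avoids this.

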### Power analysis

To secure adequate power for the main analysis of the intervention effect on smoking abstinence at the quit date, 3 weeks and 6 months later, we performed a priori sample size calculations using the G*Power program [63]. Based on a power of 0.80 and a two-tailed Type 1 error probability of .05, a total sample size of *N* = 128 is suitable to detect a 24% difference in smoking abstinence for the intervention group, drawing on meta-analyses of mobile-phone interventions on short and long-term smoking abstinence (RR’s between 1.7 and 2.1 [16, 17];). We assumed an abstinence rate of 27% in the control group 6 months after the self-set quit date, based on own previous studies using a highly comparable, albeit correlational, design with daily diaries around a self-set quit date in smokers and their romantic partners [64, 65]. Moreover, attrition rates between 20% (e.g., [31]) 6 months after the self-set quit date, or below 30% [15] have been reported. Thus, assuming an attrition rate of 25%, the targeted sample size is *N* = 160 smokers (*n* = 80 per group) and an additional *N* = 80 buddies.

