Following we will discuss some challenges regarding this study’s procedure. The procedure for the intervention group is very complex and complicated. Participants of the intervention group have to find a non-smoking buddy who supports them during their quit attempt and who is also willing to participate in the study. Moreover, they have to install the app and invite the buddy on their own at home to do so as well. Another aspect is that we let the participants use their own smartphones. We unfortunately have to exclude everyone who does not have an own smartphone or a mobile internet access on their own smartphone. However, results of a representative report showed that 100% of adolescents and their families have at least one smartphone at home and thus, coverage of smartphones in Switzerland is very high [70]. At the same time, our population of interest are individuals that can potentially use the app. Using one’s own smartphone in everyday life moreover has the advantage of ensuring a relatively natural setting for the intervention, hence, increasing ecological validity. Furthermore, we are not able to control the intervention fidelity in terms of using the mobile application if participants will not give us permission to access and use the usage data or if participants will use other channels like text messages to chat about the smoking cessation instead of the SmokeFree Buddy app. Finally, there is a trade-off between assessing abstinence rates with the iCO Smokerlyzer, a state-of-the-art objective ambulatory assessment measure, and its antecedents by self-report. Moreover, there exists the possibility of confounding effects of the ambulatory assessment with the buddy social support intervention. Reporting on their own smoking and measuring the smoking behavior also objectively with their own smartphone can be in itself a self-monitoring intervention for the participating smokers. However, this effect of the self-reports and the objective measure of CO is constant between the intervention and the control group and we are especially interested in the effect of the SmokeFree Buddy app over and above the self-monitoring component. Another important point concerns the successful recruitment of smokers. Besides that smokers need to be willing to participate in an intensive longitudinal study, smokers participating in the present study have to meet many inclusion criteria such as smoking at least one cigarette per day, having the intention to quit smoking etc. Therefore, the recruitment process can be very challenging as already experienced by researchers investigating smokers’ everyday life in an intensive longitudinal design (c.f, [26, 31]).

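### The sample size treats dropouts as leaving the analysis, but the analysis keeps them as smokers, so the 6-month power is about 71% or about 88%, depending on an unstated scale

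*Protocol article*

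**What the plan says.** The Power analysis section sets the design values: "Based on a power of 0.80 and a two-tailed Type 1 error probability of .05", a total of 128 described as "suitable to detect a 24% difference in smoking abstinence for the intervention group", and a control rate, "We assumed an abstinence rate of 27% in the control group 6 months after the self-set quit date". The intervention rate is therefore 51%. The section then reports attrition of 20% in one earlier study and below 30% in another source, and continues: "Thus, assuming an attrition rate of 25%, the targeted sample size is" 160, or 80 per group.

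The Statistical analysis section applies intention-to-treat to all analyses. It gives intermittent gaps to maximum likelihood and sets a separate rule for complete dropout: "Participants who completely drop out of the study will be treated as smokers".

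The Discussion says of the intervention group only: "The procedure for the intervention group is very complex and complicated". These participants must find a willing non-smoking buddy, install the app and invite the buddy themselves. The Control group section gives that group the same setting without the app.

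**The concern.** Recruiting extra participants to cover attrition is a full remedy only when dropouts are removed and the rates among those analysed stay as planned. When dropouts are coded as smokers, nobody is removed. Attrition then reduces the difference being tested, and an inflation sized for lost numbers does not restore the planned power. The two sections therefore describe different analyses, and the article does not say whether the 27% and 51% already include dropouts as smokers.

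At stake is whether the trial has the power it claims for a primary outcome at 6 months. A second consequence follows from the same rule. If dropout differs between groups, the coding carries that difference straight into the estimated effect.

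**Working it through.** **Inputs from the Power analysis section.** Control 27%; difference 24 points, so intervention 51%; two-sided 5%; attrition 25%, with 20% to below 30% as the reported range (30% is used below as its upper limit); 80 per group. Allocation is 1:1 (Randomization section).

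**Formula.** Two-proportion test with pooled variance under the null and no continuity correction. With m the mean of the two rates and n per group:
- s0 = √(2m(1−m)/n)
- s1 = √(p1(1−p1)/n + p2(1−p2)/n)
- power = Φ((|p2−p1| − 1.96·s0)/s1)

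**1. Reproduce the plan's figure.** With n = 64, p1 = 0.27, p2 = 0.51: s0 = 0.0862, s1 = 0.0836, power = Φ(0.85) = 80.2%. Solving for n gives 64 per group, 128 in total. The stated number reproduces.

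**2. Reproduce the inflation.** 128 × 1.25 = 160. After 25% attrition, 160 × 0.75 = 120 remain, 60 per group, not 64. Dividing instead gives 128/0.75 = 171. With dropouts simply removed, power at 60 per group for 27% vs 51% is 77.6%.

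**3. Apply the smoker rule to rates among those retained**, with equal dropout and all attrition complete. At 25%:
- 0.27 × 0.75 = 0.2025 and 0.51 × 0.75 = 0.3825, a difference of 18 points
- n = 80: s0 = 0.0719, s1 = 0.0705, power = Φ(0.55) = 71.0%

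| Dropout, each group | Rates | Power at 80 per group | n per group for 80% |
|---|---|---|---|
| 20% | 21.6% vs 40.8% | 75.0% | 91 |
| 25% | 20.25% vs 38.25% | 71.0% | 100 |
| 30% | 18.9% vs 35.7% | 66.7% | 110 |

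Other forms of the test at 25% give similar results: 72.3% with unpooled variance, 71.8% by exact enumeration of the Pearson test.

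**4. Split the shortfall.** From 80.2% to 77.6% is the multiplication by 1.25. From 77.6% to 71.0% is the smoker coding. Even with 86 per group (171 in total, rounded up), the coded rates give 74.1%.

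**5. The other scale.** If 27% and 51% already count dropouts as smokers, all 160 are analysed at those rates. At n = 80, s0 = 0.0771 and s1 = 0.0747, so power = Φ(1.19) = 88.3%. The 128 would then have been enough.

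**6. Unequal dropout.** The article gives no rates by group; the rates here are assumptions.
- 20% control, 30% app: 0.27 × 0.80 = 0.216; 0.51 × 0.70 = 0.357; the planned 24 points become 14.1 and power 50.5%.
- 30% control, 20% app: 0.27 × 0.70 = 0.189; 0.51 × 0.80 = 0.408; 21.9 points and power 86.4%.
- No true effect, 27% in both groups, 20% vs 30% dropout: 21.6% vs 18.9%, a false difference of 2.7 points against the app, rejected 7.1% of the time instead of 5%.
- Equal dropout leaves the rejection rate at 5%.

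**The case against.** The strongest reply is that 71% is conditional. It needs the two rates to describe people retained, and the article does not say so. On the other scale the trial exceeds its target. This stands, and it is why both figures are given. Inflating for attrition implies the first scale but does not prove it. A reader might infer that the trial is simply underpowered at 71%; the document does not support that without the condition.

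Second, the smoker rule covers only those who leave completely, and the 25% may include lesser losses. This also stands. If complete dropout were 10% (an assumption), the rates would be 24.3% vs 45.9% and power about 82%.

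Third, the extra recruits do help. Under the coded rates, moving from 64 to 80 per group raises power from 61% to 71%. The inflation repairs part of the loss, not all of it.

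Fourth, the Discussion calls the intervention procedure complex but predicts no difference in dropout, and both groups receive the same device and follow-up lottery. Unequal dropout is therefore plausible, not established, and a full analysis plan may already contain sensitivity analyses. That part is a recommendation.

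Two further readings are tempting. One is that maximum likelihood treats a skipped carbon monoxide test as uninformative about smoking. It does not: it lets missingness depend on observed data, such as the person's other days. The other is that missing carbon monoxide results should be filled from the diary. That would put self-report into the objective outcome, and nothing in the article requires it.

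**Conclusion.** The mismatch between the two sections is real, and the stated power does not match the stated analysis on either scale. On the scale of those retained, 6-month power at 80 per group is about 71% (75% to 67% over 20% to 30% attrition), with about 2.6 of the roughly 9 lost points due to the inflation arithmetic. On the scale that counts dropouts as smokers, it is about 88% and the inflation has no purpose.

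The 71% assumes that all attrition is complete dropout and equal in both groups. All the figures use the plan's own two-proportion comparison at 6 months, not the mixed logistic model or the earlier time points. Coding dropouts as smokers is not itself an error. A reader might infer that it will produce a false benefit for the app. The document does not support this: the distortion can run either way, and heavier dropout in the intervention group, the direction its extra tasks suggest, would work against the app.

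**What to change.** In the Power analysis section, state whether 27% and 51% are rates among those retained or already count dropouts as smokers. Restate the power to match the dropout rule: about 71% on the first scale, about 88% on the second. The sample size need not change. The cost is a sentence or two and, on the first scale, a less favourable stated power.

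Keep the smoker coding. As a recommended addition, unless the full plan already has it, pre-specify two sensitivity analyses: the likelihood-based model without recoding dropouts, and an analysis that varies the odds of smoking among dropouts separately by group. Report dropout by group beside them. The cost is a few extra model runs and no new data.

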### Measures

#### Smokers in the intervention and control group

The prescreening questionnaire assesses inclusion and exclusion criteria as well as measures on socio-demographics and habitual smoking behavior adapted from Keller et al. [47]. At the background assessment smokers complete a comprehensive questionnaire on current smoking, smoking history, self-regulation (e.g., smoking-specific self-efficacy, action planning, action control) [48, 49], health status [50], personality and further potential control variables. Additionally, an objective baseline measure for smoking status is taken using the mobile iCO Smokerlyzer. All three end-of-day diary phases (baseline diary, challenge diary and follow-up diary) include short scales or single items on self-reported daily smoking abstinence, number of cigarettes smoked, quantity and quality of received social support from the buddy and from other network members [26, 31, 51], quantity and quality of received social control from the buddy and from other network members [52–54], self-regulation (e.g., self-efficacy, action planning, action control) [49], indicators of subjective well-being [55], relationship quality [56] and further potential control variables. Smokers in the control group do not receive items relating to the buddy. Smokers in the intervention group additionally report on the use of the SmokeFree Buddy app. On the first day of the follow-up diary, smokers are asked to report on their smoking abstinence and lapses since their self-set quit date. During both the 28-days challenge diary and the 3-day follow up diary, all participants measure their daily smoking behavior objectively with their personal mobile iCO Smokerlyzer.

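### The outcome models as stated leave out cigarettes per day recorded before allocation, and the planned baseline significance test is uninformative; adjusting would add about 0 to 5 points of power

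*Protocol article*

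**What the plan says.** All places are in the protocol article.

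- **Statistical analysis, model terms.** "Daily smoking abstinence will be modeled as a function of time group and group by time". Models 1 and 2 differ only in where time is centred (quit date, three weeks later). Model 3 is a separate group comparison at six months. The cigarette count gets a zero-inflated negative binomial model. No baseline covariate is named for any of these.
- **Statistical analysis, preliminary step.** "Preliminary analysis will include a randomization check to test for baseline differences between intervention and control participants". The section does not say what follows from a significant or non-significant result.
- **Measures, smokers in both groups.** All three diary phases, including the baseline diary, record the number of cigarettes smoked. At the lab visit "smokers complete a comprehensive questionnaire on current smoking, smoking history, self-regulation" and other items, and a CO reading is taken.
- **Methods/design and Randomization.** The baseline diary is finished before participants are invited to the lab. The numbered envelope is opened on the day of the lab visit. Allocation is 1:1 in blocks of 4, 6 or 8, with no mention of stratification by smoking level. Entry requires at least one cigarette a day, with no stated upper limit.

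**The concern.** Baseline consumption is a plausible predictor of whether a smoker quits, and for the secondary outcome it is the outcome's own baseline value. The entry criterion admits light and heavy smokers alike, and nothing in the allocation scheme balances them, so the arms can differ by chance. A covariate fixed in advance would deal with that and could sharpen the treatment comparison. As stated, the models do not use it.

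The baseline test does not fill this gap. Under concealed random allocation, the hypothesis that the arms differ only by chance is true by design, so a p-value for it carries no useful information. A significant result does not show that the variable matters for abstinence, and a non-significant one does not show that an imbalance is harmless. If such tests were used to pick covariates, the adjusted estimate would depend on the data.

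**Working it through.** **1. Reproduce the plan's figure.** Inputs from Power analysis: "Based on a power of 0.80 and a two-tailed Type 1 error probability of .05"; "We assumed an abstinence rate of 27% in the control group 6 months after the self-set quit date"; the sample "is suitable to detect a 24% difference in smoking abstinence for the intervention group". Hence p0 = 0.27, p1 = 0.27 + 0.24 = 0.51 and the mean p = 0.39.

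n per arm = [z(0.975) × √(2 × 0.39 × 0.61) + z(0.80) × √(0.27 × 0.73 + 0.51 × 0.49)]² / 0.24²
= [1.960 × 0.690 + 0.842 × 0.669]² / 0.0576 = 3.666 / 0.0576 = 63.6, rounded up to 64.

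The total is 2 × 64 = 128, matching "a total sample size of *N* = 128". Power by this formula is 0.802 at 64 per arm and 0.883 at 80 per arm, the recruitment target ("assuming an attrition rate of 25%, the targeted sample size is *N* = 160 smokers"). The planned power therefore does not rely on covariate adjustment.

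**2. What is measured when.**

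| Measure | Timing relative to opening the envelope |
|---|---|
| Baseline-diary cigarettes per day | Before: the diary is completed before the lab invitation |
| Lab CO, questionnaire items | Same day; order not stated (only the app introduction is placed last) |
| Baseline abstinence | Nearly constant, since all participants smoke daily at entry; of no use as a covariate |

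**3. Gain from adjusting.** The article gives no figure for how strongly baseline smoking predicts abstinence, so I assumed an odds ratio per SD from 1.0 (no relation) to 2.5. The corresponding share of latent logistic variance is g² / (g² + π²/3) with g = ln(OR): 0.015 at 1.25, 0.048 at 1.5, 0.127 at 2.0 and 0.203 at 2.5. Each scenario had 6,000 simulated trials at a single time point, marginal rates held at 27% and 51%, and a logistic regression Wald test with and without one standardised covariate.

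| OR per SD | 64 per arm: unadjusted → adjusted | Change, points | 80 per arm: unadjusted → adjusted | Change, points |
|---|---|---|---|---|
| 1.0 | 0.813 → 0.809 | −0.4 | 0.888 → 0.886 | −0.2 |
| 1.25 | 0.807 → 0.801 | −0.6 | 0.880 → 0.884 | +0.4 |
| 1.5 | 0.809 → 0.814 | +0.6 | 0.881 → 0.893 | +1.2 |
| 2.0 | 0.806 → 0.832 | +2.6 | 0.873 → 0.900 | +2.7 |
| 2.5 | 0.815 → 0.858 | +4.3 | 0.875 → 0.924 | +4.9 |

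The Monte Carlo standard error of a power near 0.80 is √(0.8 × 0.2 / 6000) = 0.005, about half a point, so the changes at 1.0 and 1.25 are effectively nil. Under no treatment effect, rejection rates lay between 0.044 and 0.056 with and without the covariate.

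**4. What the baseline tests would show.** With k independent tests at 0.05 and sound randomisation, the chance of at least one significant result is 1 − 0.95^k. For an assumed k = 10 this is 1 − 0.599 = 0.40. The article does not give k, and smoking measures are correlated, so this is illustrative only.

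**The case against.** The strongest reply is that this is a condensed article. A covariate list normally belongs in an analysis plan, which is not shown, and the article does mention collecting further control variables. An unadjusted randomised comparison is valid, and the sample size was computed for exactly that. On this view, preferring adjustment is a matter of taste.

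Much of this stands. The plan is consistent with itself, and covariates may be listed elsewhere. But the article does state the model terms, and they contain no baseline measure; it also commits to a baseline test, which no list of covariates would make informative. A better use of data already collected is worth raising.

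The text does not support these stronger readings:

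- **The test replaces adjustment, or will select covariates.** A reader might infer this because the two sit in the same section. The article calls the check preliminary and attaches no consequence to it.
- **All baseline measures precede allocation.** This is certain only for the baseline diary. The interviewer who opens the envelope may know the allocation when CO and the questionnaire are taken.
- **Adjustment makes good any loss from attrition, or lifts power to about 86% after it.** With 25% lost, 160 × 0.75 = 120, or 60 per arm, where the unadjusted formula gives 0.776. But complete dropouts are to be counted as smokers, so 60 per arm is not the planned analysis set. Reaching 86% there would also need a covariate explaining about 30% of latent variance (odds ratio about 3.3 per SD), for which the article offers no basis.

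**Conclusion.** The point holds as a modest improvement at little cost. The stated models are valid but name no baseline smoking covariate, although one suitable measure is certainly available before allocation and is the secondary outcome's own baseline value. The planned test of baseline differences informs nothing if concealment held.

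The expected power gain is about 0 to 5 points. It exceeds 2 points only if baseline smoking is a strong predictor (odds ratio per SD about 2 or more), and the article gives no evidence on that. The figures rest on a single-time-point logistic regression. In the planned mixed model the covariate would act by reducing the between-person variance, whose size is also not given. Confidence is high on what the text states and on the lack of value of the test, and only moderate on the size of the gain.

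**What to change.** 1. Pre-specify mean daily cigarettes in the baseline diary as a fixed covariate in models 1 to 3 and in the cigarette-count model. State its form (for example linear or log) and, for the zero-inflated model, whether it enters the count part, the zero part or both.
2. Add lab CO only if it is taken before the envelope is opened, and state that order.
3. Replace the randomization check with a descriptive baseline table without p-values.
4. Because adjustment changes the conditional odds ratio, also report a standardised difference in abstinence proportions, the scale on which the 24-point target was set. In the mixed logistic model this means averaging over the random effects.

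**Cost.** No new data are needed. There is some extra programming for the standardised estimate and the count model. If the covariate turns out weak, the loss of power is negligible: at most 0.6 of a point in the simulations, which is within simulation noise.
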